## 11.2 Infusion pump

### 11.2.1 TME-participants

Naloxone (3.25 mg/kg) or placebo will be administered i.v. on Day 1 and Day 2, according to the randomization procedure. A syringe (IVAC®) will be filled with a 100 ml solution of either naloxone 4 mg/ml or placebo and inserted into the pump (IVAC® P7000 syringe based pump).

### 11.2.2 BI-participants

Naloxone (3.25 mg/kg) will be administered i.v. on the study day. A syringe (IVAC®) will be filled with a 100 ml solution of naloxone 4 mg/ml and inserted into the pump (IVAC® P7000 syringe based pump).

## 12. SIDE EFFECTS

### 12.1 Side effects/Adverse events (AEs)

Side effects are defined as any harmful and unwanted event, sign or symptom, which occurs during the participation in the study and which is time related with the administration of the study drug, regardless of being considered to be caused by the study drug or not. All adverse events will be recorded in the participants' Case Report Form. If an adverse event occurs more than 6 hours after the last drug administration and there is no apparent causal connection or association with the study drug, it will not be considered an adverse event.

Start and end date & time, severity and impact of all the adverse events must be registered. The severity of the adverse event and its relationship to the study drug must be evaluated in accordance with the guidelines below.

*Guidelines for classification of Adverse Events possibly related to the study*

1. **Not related** – there is no temporal relationship; other etiologies are very likely.
2. **Possibly related** – correlation between study drug administration and adverse events is less clear; other etiologies are also possible.

3. **Probably related** – there is a clear temporal relationship between study drug administration and adverse events with improvement of the adverse event after discontinuing the study drug; participant's clinical condition does not explain the adverse event reasonably.
4. **Related** – there is a clear temporal relationship between study drug administration and adverse events.

Participants, experiencing adverse events, will be monitored with appropriate clinical evaluation and laboratory tests as indicated by the responsible physician. All participants with adverse events will be followed until satisfactory recovery or stabilization are attained.

A Serious Adverse Event (SAE) is not dose-dependent and results in a significant risk of death or disability for the participant, including, but not limiting itself, to an event that:

1. causes death.
2. is life-threatening - the participant was at imminent risk of dying from the adverse event, according to the investigator's assessment.
3. requires hospitalization or prolongs already occurring hospitalization.
4. causes permanent disability.

The Summary of Product Characteristics of Naloxone published at the homepage of Danish Health and Medicines Authority will be used as a reference document, in case a serious adverse event has to be evaluated as expected or non-expected.

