### **4.2.2 Burn injury (BI-participants)**

#### *4.2.2.1 Adverse effects*

The first degree burn injury is a moderately painful procedure inducing signs of a slight sunburn with erythema, hyperemia, hyperalgesia and hypersensitivity. These signs subside in most cases 24 to 48 hrs, without leaving residual signs. However in 1-2% of participants hyperpigmentation is evident.

If the participant experiences severe pain during induction of the burn injury the participant is able to discontinue the heating by pushing a button terminating the stimulus or by saying so to the investigator. In case of a malfunctioning, overheating contact thermode a more severe second to third degree burn injury has been described. Due to the rigorous, compulsory testing paradigms of our thermodes, we have not experienced any thermal adverse effects during the last five years with the BI-model (H-2-2010-115; H-2-2012-036; H-2-2012-174; H-1-2013-045; H-4-2013-013), including more than 350 burn injuries.

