## 6.2 BI-participants

|                |                                                         |
|----------------|---------------------------------------------------------|
| Study type:    | Randomized, placebo-controlled, double-blind crossover  |
| Randomization: | Computer generated randomization list, closed envelopes |
| Phase:         | Phase 2                                                 |
| Blinding:      | Double-blind, crossover                                 |
| Subjects:      | Healthy volunteers                                      |
| Number:        | Day 0: 80 subjects; Day 1-4: 40 evaluable subjects      |

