#### 9.1.2.2 Burn injury days: Day 1 (right leg)/Day 3 (left leg; [Figs. 3 and 4]):

- The participants have been instructed to use a hair trimmer in the test areas on both lower legs, two days before each study session.
- It is verified that the participant belongs to either the low-sensitizer group or the high-sensitizer group.
- Urine-sample to test for opioids (sample is discarded just after the analysis).
- **Baseline assessments**, as previously described (Day 0; Fig. 4).

- **Burn injury induction**, as previously described (Day 0; Fig. 4).
  - **Post-injury assessments**, as previously described (Day 0; Fig. 4). However, an additional 2 hrs post-injury assessment is made at **time 2 hrs 7"** after induction of the burn injury (cf. 9.2.5.2), using a **green** marker.

[figure not shown]

**Fig 3.** General study layout for the burn injury (BI) study. BIs are induced Day 0, Day 1 and Day 3. Day 0 is a screening day, including high-sensitizers (large secondary hyperalgesia areas; 75% quartile) and low-sensitizers (small secondary hyperalgesia areas 25% quartile). Day 1 and Day 3 include induction of BIs in high- and low-sensitizers. Target-controlled-infusion (TCI) days are Day 2 and Day 4, with randomized allocation between placebo and naloxone. The time line between Day 1 and Day 2, and, Day 3 and Day 4, is 7 days. The timeline between Day 3 and Day 0 is 8 weeks or more.

[figure not shown]

**Fig 4.** Study layout for the burn injury (BI) study. Day 1/Day 3 includes induction of BI (mild thermal injury; 47C°, 7") with baseline assessments (green rectangle), burn injury (red) and post-injury assessments (blue). Day 2/Day 4 include a pre-drug assessment (blue; post-injury 165 hrs), drug-infusions (naloxone or placebo; 167-168 hrs) and assessments during target-controlled-infusion ([TCI]; light green). The estimated plasma concentrations are superimposed in dashed red line. Roman numerals indicate the three TCI-steps. Stars indicate assessments of pin-prick pain thresholds (red), and secondary hyperalgesia areas (green star).

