  - **Time 168 hrs 35" to 170 hrs 20":** observation period where the participant is allowed to drink, eat and begin to ambulate. Monitoring is continued until **169 hrs 00"**. The peripheral i.v. cannula is removed at **169 hrs 00"**.
  - **Time 170 hrs 20":** the participant is discharged

The participants will be contacted by phone [name] the day after each examination day to check up on potential side effects. The examiner [name] will be on call on mobile at the request of the participant for 24 hrs after each examination day.

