### 13.1.2 BI-participants

Data from our previous high-dose naloxone study (Pereira MP et al [2015] PLOS One 10: e0134441. 10.1371/journal.pone.0134441 [doi]) indicate:

1. for the high-sensitizers ( $n = 3$ ): secondary hyperalgesia areas 168 hrs after the BI during placebo infusion, mean (SD),  $2.1 \text{ cm}^2$  ( $2.5 \text{ cm}^2$ ) and during naloxone infusion  $111.0 \text{ cm}^2$  ( $26.3 \text{ cm}^2$ ).
2. for the low-sensitizers ( $n = 3$ ): secondary hyperalgesia areas 168 hrs after the BI during placebo infusion,  $0.3 \text{ cm}^2$  ( $0.1 \text{ cm}^2$ ) and during naloxone infusion  $0.9 \text{ cm}^2$  ( $0.6 \text{ cm}^2$ ).

Using the significance level  $\alpha$  set to 0.01 and the power set to  $= 0.90$  ( $\beta = 0.10$ ), the estimated number of individuals needed to reject the null hypothesis in the high-sensitizers are 5 (effect size 4.1; sic!) and in the low-sensitizers are 18 (effect size 1.4). Since the data used for sample size estimates are made on an extremely limited number of individuals, and, since the study of nature is a proof-of-concept, it was decided to include 20 high-sensitizers and 20 low-sensitizers. Boot-strapping techniques could have been used, but we considered the number individuals used in the sample estimate too extreme. On the other hand, if a larger number of subjects are needed, the clinical significance is deemed of dubious value.

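### The adverse-event definition is tied to study-drug timing, so no rule requires a non-serious burn harm to be recorded, although all 160 planned burns fall on non-drug days

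*Protocol*

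**What the plan says.** **Definition.** Section 12.1 gives a single definition under a heading that joins side effects and adverse events. The event must occur during participation and must be one "which is time related with the administration of the study drug", whether or not the drug is thought to be the cause. A later sentence, starting "If an adverse event occurs more than 6 hours after the last drug administration and there is no apparent causal connection", takes such late events out of the category.

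**Classification.** The four-level causality scale in 12.1 is framed around the study drug, and so is the instruction in 12.2 to establish relatedness. The naloxone product summary is the expectedness reference. Section 12.3 requires reporting of significant side effects caused by drugs given in the study. Section 12 does not mention the burn.

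**Burn harms.** Section 4.2.2.1 says the ordinary signs subside in most cases in 24 to 48 hours, then adds: "However in 1-2% of participants hyperpigmentation is evident". For a malfunctioning device it says: "overheating contact thermode a more severe second to third degree burn injury has been described".

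**Schedule.** The legend of Fig. 3 states "BIs are induced Day 0, Day 1 and Day 3" and places the infusions on Days 2 and 4, each 7 days after a burn. Section 6.2 gives the numbers: "Day 0: 80 subjects; Day 1-4: 40 evaluable subjects". Under 9.1.2, volunteers who are neither high- nor low-sensitizers leave after Day 0.

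**Follow-up.** Section 9.1.2.3 provides a phone call "the day after each examination day to check up on potential side effects". The instruction to log side effects continuously stands only in the infusion-day agendas.

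**The concern.** The burn is a deliberate tissue injury in healthy volunteers and the only study intervention given to all 80 of them. The protocol foresees specific harms from it, then defines recordable events by the timing of a different intervention. A lasting mark or a blister from a burn has no required place in the adverse-event record. If someone does write it down, the scale offers no way to say that a study procedure caused it. A final report built on section 12 could understate the harms of the burn model. The commitment in 12.1 to follow participants until recovery or stabilization attaches to adverse events, so it would not clearly extend to these harms either.

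**Working it through.** **1. Reproduce the plan's own figures.** Section 13.1.2 says "it was decided to include 20 high-sensitizers and 20 low-sensitizers": 20 + 20 = 40, matching section 6.2. Section 5.2.2 gives 1.5 h (Day 0), 5 h (Days 1 and 3) and 11 h (Days 2 and 4): 1.5 + 5 + 11 = 17.5 h, matching its stated total. Screening, burn days and infusion days are therefore separate.

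**2. Count burns against drug days.** The protocol states no total.

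| Day | Burns | Drug given | Position relative to drug |
|---|---|---|---|
| 0 | 80 | no | before any dose |
| 1 | 40 | no | before any dose |
| 3 | 40 | no | after the Day 2 infusion, 7 days before Day 4 |

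Total: 80 + 40 + 40 = 160. On a drug day: 0. Before the volunteer's first dose: 80 + 40 = 120. The infusion starts 167 h 20 min after the burn (9.1.2.3).

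**3. Volunteers burned but never dosed.** 80 - 40 = 40. This is a planned figure. If the cut-offs really are the quartiles, so that each volunteer has a one-half chance of passing, the 95% binomial range for the number passing is 31 to 49. The number screened out would then also run from 80 - 49 = 31 to 80 - 31 = 49.

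**4. Expected hyperpigmentation at the protocol's 1-2% of participants.** Expected cases = n × p; chance of at least one = 1 - (1 - p)^n, taking participants as independent.

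- All 80: 80 × 0.01 = 0.8 to 80 × 0.02 = 1.6. Chance of at least one: 1 - 0.99^80 = 55% to 1 - 0.98^80 = 80%.
- The 40 never dosed: 0.4 to 0.8. Chance of at least one: 1 - 0.99^40 = 33% to 1 - 0.98^40 = 55%.
- With 31 to 49 screened out: 31 × 0.01 = 0.31 to 49 × 0.02 = 0.98 cases.

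**5. Would the follow-up reveal it?** Section 5.2.2 calls Days 0 to 4 all examination days, so the next-day call can be read as covering Day 0. It comes before or within the 24-48 h in which normal signs subside, so a lasting mark cannot yet be told from the expected reaction. No later contact is planned for those screened out. After Days 1 and 3, the same leg is re-tested at 165 h on Days 2 and 4, including pin-prick thresholds in the burned area. The agendas list no record of skin appearance at those visits, or at the Day 0 left-leg site before the Day 3 burn.

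**The case against.** The strongest reply is that section 12 is less closed than its definition. Each part has some force.

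- **Serious harm.** A reader might infer that a severe burn would go unreported. The text does not support that. The serious-event definition in 12.1 carries no drug-timing condition, and 12.3 requires immediate reporting of any situation that may affect participants' safety. A second- or third-degree burn could reach the sponsor and the authorities by either route.
- **Causality.** A reader might infer that a burn harm has no category at all. It has one: *Not related*, described by the absence of a temporal link. But this category sits awkwardly with a definition that demands such a link, and it would label harm caused by the study as unrelated.
- **Examination of the site.** It would be wrong to say that nobody looks at the burn again. Day 1 and Day 3 sites are tested a week later, and the Day 0 site goes through baseline testing before the Day 3 burn. What is missing is a recorded finding on the skin.
- **Contact.** Calls after each examination day, and an examiner on call for 24 hours, could pick up an acute problem, even on Day 0. This stands for acute events and does not help with late marks.
- **The 6-hour sentence.** It runs from the last dose, so it cannot exclude the 120 burns made before any dose. It bears only on the 40 Day 3 burns.
- **Wording.** Sections 12.2 and 12.3 speak of identifying and recording all adverse events, and an investigator might record burn harms on that basis. The only definition supplied still points the other way.

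**Conclusion.** The point holds for non-serious burn harm. The protocol lists such harms, places all 160 burns outside drug days, and defines and classifies adverse events by the drug. No rule requires these harms to be recorded, and any that are recorded can be related only to the drug. The expected size is small: 0.8-1.6 hyperpigmentation cases among 80 volunteers, including 0.4-0.8 among about 40 whose last possible contact is a next-day call.

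This rests on planned counts (40 is the evaluable number, so replacements would add burns) and on the protocol's 1-2% applying per participant whatever the number of burns. For thermode injury, the record of none in more than 350 burns gives an upper 95% limit of 1 - 0.05^(1/350) = 0.85% per burn, or 160 × 0.0085 = 1.4 events. That is a bound and not an expected count, and the conclusion does not depend on it.

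A reader might go further and infer that the final report would show no burn harm whatever happened. The serious-event route, the general reporting duty and the later visits all contradict that. No efficacy estimate is affected.

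**What to change.** - In 12.1, define an adverse event as any untoward event from consent to end of participation, whether or not it is time-related to study drug. Reconcile the 6-hour sentence and the *Not related* category with that definition.
- Add a second causality field for relatedness to study procedures (burn, cannulation, sensory testing).
- In the BI case report form, add a field for burn-site appearance at the existing Day 2 and Day 4 visits and, for the Day 0 site, before the Day 3 burn.
- Optionally, send one later message to volunteers screened out after Day 0, to cover late marks.

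The cost is protocol wording, two extra form fields and, if the option is taken, about 40 short messages. The reported event count will be slightly higher. No visit, dose or infusion schedule changes.

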## **12.3 Reporting of AEs and SAEs**

The investigator has the responsibility to ascertain that all adverse events will be recorded and appropriately documented in the participant's Case Report Form. The Sponsor is responsible for the continuous evaluation of the study risk/benefit ratio. If a situation arises, that may affect the participants' safety or that affects the ethical integrity of the study, it must be immediately reported to the Danish Health and Medicines Authority. A similar report must be sent to all the involved investigators and to the regional Research Ethical Committee.

Furthermore, the following rules for reporting to authorities should be taken into account. Any significant side-effect caused by drugs given in the study – the experimental treatment, comparison

drugs or placebo – must be reported. The sponsor has to be kept informed by the investigator of adverse events. The final report of the study should contain a description of all observed side effects.

SAEs must be reported immediately by the investigator to the sponsor and in addition a report on participants' safety should be sent once per year to the Research Ethical Committee.

**Serious adverse reactions (SARs)** (Serious, suspected adverse reactions), and in addition a report on participants safety, should be reported by the sponsor once per year to the Danish Health and Medicines Authority.

The sponsor must immediately report unexpected and **serious suspected adverse events (SUSAR)** to the Danish Health and Medicines Authority. Summary of Product Characteristics of naloxone will be used as a reference document for evaluating whether a serious related adverse reaction is unexpected or expected. **Fatal or life-threatening SUSAR's** must be reported to the Danish Health and Medicines Authority with all relevant information including follow-up within 7 days after the sponsor became aware of them, and no later than 8 days after notification. All other unexpected and serious suspected adverse events should be reported to the same authorities within 15 days after the sponsor has become aware of them. Reports should be accompanied by comments on the consequences for the study. It is also recommended that the sponsor informs the drug manufacturer.

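### The top two causality grades in 12.1 are out of order, and the 'Not related' grade conflicts with the definition of the event being graded

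*Protocol*

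**What the plan says.** Protocol 12.1 makes the scale compulsory: the relationship of each adverse event to the study drug has to be judged by four listed categories, numbered from weakest to strongest.

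- Grade 1, *Not related*: "there is no temporal relationship; other etiologies are very likely".
- Grade 2, *Possibly related*: "correlation between study drug administration and adverse events is less clear; other etiologies are also possible".
- Grade 3, *Probably related*, asks first that "there is a clear temporal relationship between study drug administration and adverse events with improvement of the adverse event after discontinuing the study drug". It then sets one more condition, on alternative explanations: "participant's clinical condition does not explain the adverse event reasonably".
- Grade 4, *Related*: "there is a clear temporal relationship between study drug administration and adverse events", with nothing further.

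The same section defines a side effect as an unwanted occurrence during participation "which is time related with the administration of the study drug, regardless of being considered to be caused by the study drug or not". It then excludes an event that begins more than 6 hours after the last administration, provided there is also no apparent causal connection or association with the drug.

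Section 12.2 asks the medical investigator to establish the relationship. Section 12.3 uses relatedness when it speaks of "evaluating whether a serious related adverse reaction is unexpected or expected". No section adds criteria for grade 4, says which grade applies when two fit, or says which grades make an event a suspected reaction.

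**The concern.** A causality scale should ask for more evidence at each higher grade. Here the step from grade 3 to grade 4 removes two requirements and adds none. An event with suggestive timing and a good alternative explanation therefore fits the highest grade, while an event with all the supporting evidence fits grades 3 and 4 equally well.

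The lowest grade has a different problem. The event definition deliberately admits events not caused by the drug, as long as they are linked to it in time. Grade 1 is the natural place for such events, yet its wording excludes anything with a temporal link.

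What is at stake is the consistency of the safety classification and, depending on how the grades feed into 12.3, the number of serious events treated as suspected reactions.

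**Working it through.** No sample size, power or event count is involved, so the check is one of logic.

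**Inputs, all from Protocol 12.1**

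- T: clear temporal relationship to drug administration.
- D: improvement after the drug is discontinued.
- E: not reasonably explained by the participant's clinical condition.
- *Related* = T.
- *Probably related* = T and D and E.

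**Step 1: the top two grades.** Three yes/no conditions give 2 × 2 × 2 = 8 combinations.

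| T | D | E | Meets *Related* | Meets *Probably related* |
|---|---|---|---|---|
| yes | yes | yes | yes | yes |
| yes | yes | no | yes | no |
| yes | no | yes | yes | no |
| yes | no | no | yes | no |
| no | any | any (4 combinations) | no | no |

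- Meeting *Related*: 4.
- Meeting *Probably related*: 1.
- Meeting both: 1.
- Meeting *Related* only: 4 − 1 = 3.
- Meeting *Probably related* only: 1 − 1 = 0.

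Grade 3 is thus a strict subset of grade 4. Two of the three *Related*-only rows have E = no: the clinical condition explains the event, and it still fits the top grade.

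A hypothetical case under the protocol's own criteria: section 7.2.1 lets a third-molar participant enter with resting pain up to 3 and activity-related pain up to 5. Suppose pain rises during an infusion, is recorded as an adverse event, and the surgical site explains it. It fails grade 3 on E but meets grade 4 on T. The same would hold on a placebo day.

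**Step 2: the bottom grade.** Compare the two statements.

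- To be an event under the definition, it must be one "which is time related with the administration of the study drug".
- To be grade 1, it must satisfy "there is no temporal relationship; other etiologies are very likely".

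Read literally, the first excludes the second. A time-linked event with a clear other cause meets the definition and has no fitting bottom grade. The 6-hour rule does not resolve this, because it only removes late events that also lack any apparent causal link.

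**Step 3: consequence under 12.3.** The protocol does not say where the line for a suspected reaction falls, so each position is taken in turn.

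- Grades 2 to 4 count: confusing 3 with 4 changes nothing. An unreachable grade 1 means every graded serious event is suspected. The direction is over-reporting.
- Grades 3 and 4 count: confusing 3 with 4 again changes nothing, but events explained by another cause enter through grade 4. The direction is again over-reporting.
- Only grade 4 counts: a well-supported reaction filed as grade 3 could be left out. Nothing in the protocol sets the line there.

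**The case against.** The strongest reply is that this is loose wording that trained investigators would work around. The categories are headed as guidelines, and 12.2 leaves the judgement to the medical investigator. That is fair as far as it goes: the text does not show that grades will in fact be wrong. But 12.1 says the relationship must be evaluated by these categories, and gives no rule for an event that fits two of them.

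A second reply is that grade 1 can be reached. The timing requirement is attached to side effects, while the next sentence refers to adverse events. Being time-related could mean falling inside the observation window, and the temporal relationship in grade 1 could mean a plausible onset. This is a possible reading, so the conflict is established only for the literal one. Since the section uses the two event terms interchangeably, the wording still needs reconciling.

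Third, a reader might infer that serious unexpected reactions would be missed. The documents do not support that. Section 12.3 sends all serious adverse events to the sponsor immediately whatever their grade, and ties no grade to a reporting route.

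Fourth, in a double-blind crossover the drug effect on adverse events is seen by comparing naloxone days with placebo days, not through causality grades. This stands, and it limits what is at risk.

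**Conclusion.** The concern holds for the wording of 12.1. Grade 3 is a subset of grade 4, three of the four combinations that reach the top grade fail the one below it, and no other section repairs this. Grade 1 conflicts with the event definition on a literal reading. Relatedness cannot be graded consistently as the text stands.

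Several stronger conclusions might be drawn and should not be:

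- *The whole scale is inverted.* Only the top pair is out of order; grades 1 and 2 stand in the expected sequence.
- *The safety report would be unusable.* Section 12.3 asks for a description of all observed side effects and plans no summary by relatedness grade. Raw event counts by treatment day are untouched.
- *The earlier study's side-effect rate measures the problem.* Section 4.2.1.1 reports 6 of 15 participants with mild side effects, and 1 with photophobia, at 2.0 mg/kg. That counts people with any event, at a dose other than the 3.25 mg/kg planned here, and says nothing about how many would be misgraded.

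The over-reporting conclusion assumes that suspected means every grade above *Not related*, which the protocol leaves unstated. No efficacy result, sample size or efficacy analysis is affected. The point is worth correcting because the defect is plain and the correction is small.

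**What to change.** Reword the four grades in 12.1 so that they are ordered and mutually exclusive.

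- *Related*: at least all the present grade 3 criteria, plus no plausible alternative cause.
- *Probably related*: the present grade 3 criteria, where *Related* is not met.
- *Possibly related*: timing compatible with a drug effect, but another cause is also plausible.
- *Not related*: another cause is clearly more likely, whatever the timing.

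Reconcile grade 1 with the event definition, and use one term for the event throughout the section. Add one sentence stating which grades count as suspected reactions for 12.3.

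The cost is a few lines in the protocol and matching text in the Case Report Form. No extra data or visits are needed.
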